***Secondary***		
**Rate of unit nursing staff retention**	Amount of turnover (departure from the organization) experienced on each study unit while the study was conducted	Extracted from human resources records
**Patient length of stay**^**a**^	Number of days a patient spends in the hospital from the time of the order to admit to the time of discharge	Extracted from the electronic health record
**Individual components of the primary outcome:** **• Violence control intervention** **• PRN medications for behavior management** **• Nursing problem of violence risk or injurious behavior**	As above	As above
**Use of restraints**	Use of physical or chemical restraints to control patient behavior	Extracted from the electronic health record
**Use of sitters/patient attendants**	Use of sitters/patient attendants for patient observation	Extracted from the electronic health record

^a^Resource length of stay (RLOS): indicates hospital resource/bed utilization, irrespective of the change in patient status. The measure excludes the time that encounters spend as an “emergency department”-type patient but begins the instant a patient is given an order to admit as an inpatient and ends at discharge. This metric thus includes time a patient is in an emergency department bed, in the post-anesthesia care unit, or other location but has an inpatient status. The metric is viewed by average and median, and adjusted by the total Case Mix Index

### Power calculation

Approximately 17.5% of patients admitted to the two participating units required one or more of the behavioral interventions in the year prior to the study. To determine the number of months of data collection necessary to detect a reduction of 5% in the use of behavioral interventions between the intervention and control arms, we used the method described by Arnup et al. [1]. Based on patient length of stay and admit rates, we estimated between 89 and 105 patients would be eligible for inclusion each month (patients present on a unit at crossover will not be included in the analysis). Therefore, a cluster size of 90 was used. If the within-period correlation is 0.1 and the within-cluster within-period correlation is also about 0.1, we would achieve 80% power with 10 months of data collection (a total sample size of 1790 patients exposed to either the control or intervention arm). Since these estimates are based on assumptions, and it is possible that either a shorter or longer duration is needed, we have specified an interim analysis at 6 months to confirm the overall event rate and to estimate the observed correlations. No comparisons between groups will occur at this time; accrued data will be used only for sample size re-estimation.

### Data and safety monitoring and interim analysis

The study involves the collection of data to compare patients who are or who are not exposed to a clinical care practice: the behavioral intervention team (BIT). As such, there is no research intervention. The principal investigator (PI) and co-PIs, in conjunction with the clinical nursing unit leadership, clinical nurse leaders, and clinical nurse educators, will monitor for any potential impact of the study that may cause untoward impact on patients or staff on an ongoing basis throughout the study duration. If any untoward impact is observed, it will be reported to the study investigators and the Institutional Review Board (IRB).

At 6 months, the data will be reviewed to determine how many additional months of data collection will be required to have sufficient power to detect the 5% reduction in behavioral outcomes that is being designated as minimally important. Based on power calculations, 6 months is the minimum period of time for which the study can run to find this difference. At 6 months, there will be sufficient information to more precisely estimate the magnitude of the within-cluster and within-cluster within-period correlation to update the sample size estimate. Formal stopping rules for safety, efficacy, or futility have not been designated.

### Statistical analysis principles

There are two main analyses. The first will compare outcomes between patients exposed to the BIT and patients not exposed to the BIT. The outcomes are quantitative variables that are either binary or ordinal in nature. Comparisons will use logistic regression or proportional odds models, adjusted for covariates. The models will include cluster (unit) as a random effect and will also include period, including the following patient characteristics: age, sex, race, comorbidities, reason for admission, and psychiatric diagnoses.

The second analysis will compare staff perceptions between those exposed to the behavioral intervention and those not exposed to the behavioral intervention during the first month, and will also compare perceptions before exposure to the behavioral intervention with perceptions after the study concludes. We will compare categorical variables using chi-square tests, and we will compare continuous variables using paired or independent samples *t* tests as appropriate. For continuous data that are non-normally distributed, and for ordinal variables, we will use the Mann-Whitney *U* test or the Wilcoxon test as appropriate.

While our initial approach is a simple comparison, this ignores the repeated measurements. Since staff on the unit can leave and new staff can join the unit, we will use a mixed-effects model to analyze differences between before the study, at 1 month after the intervention began, and on completion of the study. Respondents will be included as a random effect. Linear, logistic, or proportional odds models will be used as appropriate for the outcome. Finally, we may model the survey outcomes using similar regression techniques to explore factors associated with changes in staff perceptions.

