### Design

The Disruptive bEhavior manageMEnt ANd prevention in hospitalized patients using a behaviORal intervention (DEMEANOR) study is a single-center, pragmatic, cluster, crossover trial, testing the superiority of the BIT program to usual care, beginning 1 March 2019 on one medical-surgical unit and one mixed cardiac care clinical unit at Vanderbilt University Medical Center in Nashville, TN, USA. The BIT is deployed to each unit in alternating months, as shown in Fig. 1. Patients presenting to the unit during a month when the team is present contribute to the intervention arm, while those presenting to a unit when the team is not present contribute to the control arm.

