### Study sites

The two study units are a 27-bed mixed cardiac medical-surgical unit and a 22-bed cardiac stepdown unit.

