### Enrollment/randomization

Patients presenting to and discharged from participating units are enrolled automatically. As a cluster, crossover trial, randomization was limited to which unit the intervention would be deployed to first. Unit nursing staff were invited to participate in online surveys by e-mail, with reminders through staff meetings; their participation is voluntary.

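### The stated patient-level model shows no unit-by-month variance component, so the BIT p-value is too small if the two units' event rates vary irregularly and separately from month to month

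*Protocol article*

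**What the plan says.** **Model (Statistical analysis principles).** "Comparisons will use logistic regression or proportional odds models, adjusted for covariates". The next sentence gives the dependence structure: "The models will include cluster (unit) as a random effect and will also include period". It then runs straight into a list of patient characteristics. It does not say whether period is categorical, fixed, random or nested in unit. No unit-by-month term, cluster-period summary or small-sample correction is named.

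**Design.** There are two clusters: "The two study units are a 27-bed mixed cardiac medical-surgical unit and a 22-bed cardiac stepdown unit". "The BIT is deployed to each unit in alternating months", so in every month one unit has the team and the other does not. The chance element is minimal: "randomization was limited to which unit the intervention would be deployed to first".

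**Sizing (Power calculation).** "Approximately 17.5% of patients admitted to the two participating units required one or more of the behavioral interventions" in the year before the study. With a 5% reduction, a cluster size of 90, one correlation of 0.1 and a second of about 0.1, "we would achieve 80% power with 10 months of data collection (a total sample size of 1790 patients" in both arms together).

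**Interim (Data and safety monitoring and interim analysis).** At 6 months the data serve to "estimate the magnitude of the within-cluster and within-cluster within-period correlation to update the sample size estimate". Two correlations are therefore treated as distinct unknowns.

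**The concern.** A unit random effect is one variance component. It makes two patients on the same unit equally correlated whether they were admitted in the same month or nine months apart. The planning sections allow those two correlations to differ; the model as worded does not.

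The omitted component is the one that matters here. The unit effect cancels from the BIT contrast because each unit spends half its months in each arm. Shared monthly movement cancels because both arms are observed every month, provided period is categorical. What is left is movement specific to one unit in one month, such as staffing, charting habits or case mix beyond the listed covariates. The protocol gives reasons to expect some. The Discussion warns of fluctuating census, changing numbers of patients with behavioral comorbidities and incomplete documentation, and Data collection describes newly added charting fields.

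Randomization offers no fallback. It chose between only two possible sequences, so the p-value rests on the model's error structure. At stake is the test of the first primary outcome, on a team that the institution plans to scale up if successful (Intervention section).

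**Working it through.** **Inputs.** From the protocol: 2 units; 10 monthly periods; m = 90 per unit-month; control rate 17.5%; total 1790 (895 per arm); correlations 0.1 and about 0.1. Assumed: two-sided α = 0.05 (not stated); the 5% reduction is 5 percentage points (17.5% to 12.5%); the two correlations are WPC (same unit, same month) and BPC (same unit, different month). The protocol's names for them differ between sections. The gap is WPC − BPC; no value is given.

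**1. The plan's sample size.**
- Individually randomized n per arm = [1.96·√(2·0.15·0.85) + 0.8416·√(0.175·0.825 + 0.125·0.875)]² / 0.05² = (0.990 + 0.424)² / 0.0025 ≈ 800, so 1600 in total.
- Design effect DE = 1 + 89·WPC − 90·BPC = (1 − WPC) + 90·gap.
- Both correlations exactly 0.1: DE = 0.90 and N = 1440 (8 months). This does not reproduce 1790.
- Back-solving: 1790/1600 = 1.119, so BPC = (9.9 − 1.119)/90 ≈ 0.0976 and the gap is about 0.0024. BPC = 0.0975 gives DE = 1.125 and N = 1800 = 2 × 10 × 90. The words about 0.1 can cover this value.

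**2. Error rate of the stated model.** With unit and categorical month, the model takes the variance factor as 1 − WPC = 0.9, whereas the true factor is 0.9 + 90·gap. The variance ratio is 1 + 100·gap, and the true type I error is 2·[1 − Φ(1.96/√ratio)]. At a gap of 0.01 the ratio is 2.0 and 1.96/1.414 = 1.386, which gives 16.6%.

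This was checked by simulating 2 units × 10 alternating months × 90 patients under no BIT effect, with 3000 to 4000 runs per setting. The model was logistic with unit, month and BIT and no patient covariates. Unit was fitted as fixed, which makes practically no difference to the BIT standard error because BIT is balanced within unit. The SD column is √(gap·0.175·0.825).

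| Gap | SD of unit-month rate (points) | Variance ratio | Type I, formula | Type I, simulated |
|---|---|---|---|---|
| 0 | 0 | 1.00 | 5.0% | about 5% |
| 0.0025 | 1.9 | 1.25 | 8.0% | 7–8% |
| 0.005 | 2.7 | 1.50 | 10.9% | 11% |
| 0.01 | 3.8 | 2.00 | 16.6% | 15% |
| 0.02 | 5.4 | 3.00 | 25.8% | 24–25% |

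**3. Which kind of drift matters.** Monthly variation shared by both units: simulated type I 4.7%. Smooth opposite linear trends: 6.4% at a total divergence of 0.8 logits and 12% at 1.6, because the alternation removes most of them. Irregular unit-specific variation does the main damage.

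**4. Candidate repairs.** Degrees of freedom: 20 unit-months − 1 (intercept) − 1 (unit) − 9 (month) − 1 (arm) = 8.
- Unit-month variance added, z test: 6.4% at a gap of 0.005, 7.5% at 0.01, 8.7% at 0.02.
- The same with t on 8 df: 1.5% at a gap of 0, rising to 4.7% at 0.02. It is conservative at small gaps because the cell variance was not allowed below its binomial value.
- Unit-month summary analysis, t on 8 df: about 4–6% at every gap.

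**5. Power at 1790.** SE = √(0.25375/895 · DE), where 0.25375 = 0.175·0.825 + 0.125·0.875.

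| Gap | SE | Power, z | Power, t on 8 df |
|---|---|---|---|
| 0 | 0.0160 | 88% | 78% |
| 0.0025 | 0.0179 | 80% | 69% |
| 0.005 | 0.0196 | 72% | 61% |
| 0.01 | 0.0226 | 60% | 50% |
| 0.02 | 0.0277 | 44% | 36% |

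These figures rest on WPC = 0.1. A simulation with a smaller difference between units gave 71%, 57%, 47% and 37% for the 8-df analysis at gaps of 0, 0.005, 0.01 and 0.02.

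**The case against.** **The sentence is condensed, and fuller documents may exist.** If period was meant as a random effect nested in unit, the component is present and the objection to the model falls. That stands as a reason to clarify. It does not remove the point: the article chose to state the dependence structure, and a plain reading gives unit alone as random.

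**The model agrees with the planning values.** If the two correlations are equal, the model is valid, and the protocol puts them at 0.1 and about 0.1. This also stands. A reader might infer that the p-value is wrong in any event; the documents do not support that. But equality gives 1440 patients rather than 1790, and the stated size fits a small non-zero gap.

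**Drift.** A reader might infer that any month-to-month movement inflates the error. It does not: shared movement is absorbed by categorical period, smooth opposite trends matter less, and the listed covariates may remove part of the case-mix variation. The simulations had no covariates, so the gap should be read as what remains after adjustment.

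**Scope.** A reader might extend the point to every patient-level secondary outcome. Treatment of outliers says that length of stay and counts will generally be handled non-parametrically, so this model does not clearly govern them.

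**Conclusion.** The point holds in conditional form. As worded, the model carries no unit-by-month variance, which the power and interim sections treat as a separate unknown and which drives the error of a contrast that switches by unit-month. If the units' rates vary irregularly and separately, the BIT standard error is too small and its interval too narrow. The false-positive rate is nominal at a gap of 0, about 8% at the gap implied by the plan's own sample size, and 15–17% at 0.01, where a unit-month's rate has an SD of only 3.8 points.

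This rests on two-sided 5%, an absolute 5-point effect, categorical period, no random period within unit, and a gap that the documents do not give. The 0.0025 gap is a back-solve, not a stated input.

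**What to change.** State the model for the first primary outcome as follows: unit (2 levels) and month (10 levels) as fixed effects, patient covariates, a random intercept for unit-by-month (20 cells), and the BIT effect tested with t on 8 df. The random intercept with a z test is not enough. Alternatively, compute the covariate-adjusted between-unit difference in each of the 10 months and regress it on arm with t on 8 df; this held closest to 5%. If a random period within unit was already intended, say so and add the small-sample reference. Use the same approach for the binary and ordinal patient-level secondary outcomes analysed with this model.

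Restate the power claim with the between-period correlation and the test used, and report the correlations estimated at 6 months.

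**Cost.** Text and code change, but so does precision. Intervals widen, and on 8 df power is below 80% even at a gap of 0. Trial status reports that enrollment has ended, so the lost power cannot be regained by adding months. A non-significant result would have to be read with that in mind.

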## Background

Patients who are hospitalized on non-behavioral health units who exhibit concurrent psychiatric comorbidities can be at risk for increased length of hospital stay due to the complexities associated with treatment, as well as behaviors that can be difficult to address by staff. Research has substantiated that 20–40% of patients hospitalized on general medical-surgical units have a psychiatric diagnosis [4, 7]. At our institution, 54% of all discharges on two medical-surgical units during fiscal year 2017 had a behavioral health diagnosis. These patients had a 25% longer mean length of stay (6.6 days vs 5.31 days without a behavioral health diagnosis) and 17% higher mean variable costs per discharge ($11,307 vs $9642), based on 104,843 total patient days.

At the same time, an internal “Behavioral Health Care Knowledge and Skills” assessment of 623 staff nurses identified that 72% reported patients’ behavior impacted their ability to provide care, 58% reported experiencing situational anxiety in caring for these patients, 56% reported caring for behavioral health patients daily to weekly (32% reported monthly), 50% reported feeling somewhat to very uncomfortable caring for these patients, and 44% feared for their personal safety as a result of patient disruptive behavior. These data demonstrate a large impact of patient behavior on the care that can be provided to them and on the satisfaction and morale of nursing staff.

Additionally our institutional data suggest nursing turnover rate is higher for those units with a higher burden of patients with behavioral comorbidities, and exit interviews suggest a link between turnover and the challenges of managing patients exhibiting disruptive behavior. Beyond turnover, there is considerable transfer from these units as nurses seek to improve their job satisfaction. Given the impact on patient care as well as on those providing care, identifying effective strategies for preventing and managing disruptive patient behavior has become a priority in promoting staff and patient safety.

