### Intervention

The integration of the BIT into the unit is not itself a research intervention. Institutional leadership planned to deploy one team as a demonstration project, and to scale it if successful. This provided an opportunity for rigorous evaluation of the team’s effectiveness. The BIT, a multidisciplinary team comprising a psychiatric-mental health advanced practice nurse and a clinical social worker, with psychiatrist consultation as needed, is a modified version of an established model at Yale New Haven Hospital [14]. The team proactively screens patients upon admission to the unit, utilizing a protocol which includes a comprehensive chart review and, if indicated, a brief interview, seeking to identify those patients who possess risk factors indicative of either a potential psychological barrier to their own clinical progress or a potential risk for exhibiting disruptive, aggressive, or self-injurious behavior during their hospitalization. Once identified, the team provides interventions aimed at mitigating these risks through a variety of patient-specific interventions, including:
Psychiatric consultation and recommendations for symptom managementBehavioral plans of care for nurse/patient interactionPsychosocial support and brief psychotherapeutic interventionCurbside consultation for any member of the patient’s healthcare teamPatient advocacy and care coordinationPsychiatric-specific disposition support, including both inpatient and outpatient psychiatric services.

The team also provides education and support to the patient care teams (nurses, physicians, and others) and assists non-psychiatric staff in the management of patients who require behavioral healthcare.

All patients on a unit when the BIT is present will be eligible for BIT services, including those who are already admitted when the team crosses into the unit. During a month when the BIT is not present on a unit, the care and management of patients is not supported with proactive screening and management. Unit staff have access to all psychiatric or behavioral care routinely available in usual care. To ensure continuity of care, patients who continue to require psychiatric support at the time the BIT rotates off the unit will continue to receive care equivalent to the usual care condition. It is anticipated that monthly rotations will occur for 10 to 12 months.

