### Data collection

Data are being collected for patients and for unit staff. Patient information is documented as a component of usual clinical care, and those data needed for this study will be extracted from the electronic health record (EHR). Data include demographics, documentation of patient disruptive behavior and associated medication administration, and patient length of stay. Disruptive behavior was not previously specifically defined as part of routine clinical care, and documentation in the clinical chart was variable. As part of the study, new documentation fields were added to the EHR to enable description (and subsequent extraction) of specific patient behaviors. Disruptive patient behavior will be documented, including physical behaviors (hit, kick, slapped, shoved, spit at, thrown objects, grabbed, bitten, or attacked), verbal behaviors (threatening, bullying, harassing, name calling, blaming, insulting, yelling, cursing, intimidation), and any clinical interventions that are implemented to control any violent behavior.

Data will be extracted from the EHR by an automated query. The query will be validated by manual cross-check of a subset of cases. Data will be identified using an encounter number, allowing for merging of data for individual patients from different sources. The data files generated by manual query will be stored on secure servers and will be merged into a single dataset for analysis by the statistical team.

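### The patient-outcome model adjusts for psychiatric diagnoses with no cut-off date, although BIT months look harder for them; if more are recorded in BIT months, the adjusted odds ratio is biased towards the BIT

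*Protocol article*

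**What the plan says.** All references are to the protocol article.

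- **Statistical analysis principles.** For the comparison of exposed and unexposed patients: "Comparisons will use logistic regression or proportional odds models, adjusted for covariates". Unit enters as a random effect, period is included, and the patient covariates are "age, sex, race, comorbidities, reason for admission, and psychiatric diagnoses". No date or source is given for the last of these, or for comorbidities, which may include psychiatric conditions.
- **Data collection.** "Patient information is documented as a component of usual clinical care", and the study extracts what it needs from the electronic health record (EHR).
- **Intervention, BIT months.** "The team proactively screens patients upon admission to the unit", "utilizing a protocol which includes a comprehensive chart review and, if indicated, a brief interview". The team includes a psychiatric-mental health advanced practice nurse, with a psychiatrist as needed. Psychiatric consultation is one of its listed services.
- **Intervention, control months.** "the care and management of patients is not supported with proactive screening and management". However, "Unit staff have access to all psychiatric or behavioral care routinely available in usual care".
- **Background.** As institutional context, "54% of all discharges on two medical-surgical units during fiscal year 2017 had a behavioral health diagnosis".

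**The concern.** Age, sex and race cannot be altered by which arm a patient is in. A psychiatric diagnosis written into the record during the stay can be, because the arms differ by design in how actively psychiatric problems are looked for. If the EHR query picks up every diagnosis attached to the encounter, the model conditions on something that exposure may have changed.

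The mechanism is simple. Suppose some patients with an unrecognised condition gain a recorded diagnosis in BIT months but would not have done so in control months. In BIT months they leave the undiagnosed stratum, which then contains fewer high-risk patients. If their risk is below that of patients already diagnosed, they also dilute the risk in the diagnosed stratum. Within strata the BIT arm then looks better than the control arm, even if the team prevents nothing.

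Randomising which unit received the team first does not protect against this, because the imbalance arises after exposure. At stake is the estimate for the first primary outcome.

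**Working it through.** The article gives no figure for this effect, so there is none to reproduce. The benchmark is its planned effect.

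**Benchmark.** Power calculation section: 17.5% of patients needed an intervention in the prior year, and the aim is to detect a 5% reduction. Read as percentage points (17.5% to 12.5%), the target odds ratio (OR) is (0.125/0.875) / (0.175/0.825) = 0.1429 / 0.2121 = 0.67.

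**Inputs from the article**
- Event rate 17.5%, applied to both arms (no BIT effect).
- Diagnosed share in control months 54%. This is the Background figure, borrowed as a plausible prevalence; it is not tied to the model covariate.
- 1790 patients, taken as 895 per arm. This affects only the rejection rates.

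**Assumed inputs**
- Event risk with a diagnosis: 22%, 25% or 28%. The risk without one follows from the 17.5% total. For 25% it is (0.175 − 0.54 × 0.25) / 0.46 = 0.040 / 0.46 = 8.7%. For 22% and 28% it is 12.2% and 5.2%.
- Share of all patients newly labelled in BIT months only: 3%, 6% or 10%.
- Event risk of the newly labelled: equal to the undiagnosed, average (17.5%), equal to the diagnosed, or 40%. Combinations that would need negative event counts were dropped.

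**Worked case: 25% against 8.7%, 6% newly labelled at 17.5% risk.** Shares of each arm:

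| | Control: share, events | BIT: share, events |
|---|---|---|
| Diagnosis | 0.54, 0.1350 (25.0%) | 0.60, 0.1350 + 0.06 × 0.175 = 0.1455 (24.3%) |
| No diagnosis | 0.46, 0.0400 (8.7%) | 0.40, 0.0400 − 0.0105 = 0.0295 (7.4%) |
| Total | 0.1750 | 0.1750 |

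The crude OR is exactly 1.00. The Mantel-Haenszel OR over recorded diagnosis is the sum of (BIT events × control non-events / stratum size) divided by the sum of (BIT non-events × control events / stratum size):

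- Diagnosis stratum: 0.1455 × 0.4050 / 1.14 = 0.0517, and 0.4545 × 0.1350 / 1.14 = 0.0538.
- No-diagnosis stratum: 0.0295 × 0.4200 / 0.86 = 0.0144, and 0.3705 × 0.0400 / 0.86 = 0.0172.
- OR = 0.0661 / 0.0711 = 0.93.

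Logistic regression of outcome on arm and recorded diagnosis, fitted to the expected cell counts, also gives 0.93. If the newly labelled carry 25% risk instead, the OR is still 0.93.

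**Full grid.** Same logistic model, no true effect:

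| Newly labelled in BIT months only | Adjusted OR | Chance of a significant result favouring the BIT (nominal 2.5%) |
|---|---|---|
| 0% | 1.00 | 2.5% |
| 3% | 0.95–0.98 | about 4–6% |
| 6% | 0.89–0.96 | about 5–14% |
| 10% | 0.84–0.94 | about 7–28% |

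The OR was below 1 in every feasible combination, whatever the risk of the newly labelled patients. The last column assumes a two-sided 0.05 test and leaves out unit, period, clustering and the other covariates, so it is illustrative only.

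**The case against.** The strongest reply is that the article is silent on timing rather than wrong. It calls the covariates patient characteristics and lists psychiatric diagnoses beside age, sex, race and reason for admission. Elsewhere it speaks of baseline characteristics by group. Look-back windows and code lists usually belong to a fuller protocol or analysis plan, which may already contain the restriction. Adjusting for psychiatric history is also reasonable with two units and only the order randomised.

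Much of this stands. But the article does fix the covariate list, and in a trial of psychiatric screening this covariate is unusually open to influence from the intervention. Whether it is dated before or after exposure decides whether the adjustment is valid.

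Four stronger readings may tempt a reader, and the article does not support them:

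- *The BIT enters diagnoses.* The article says neither that it does nor that it does not. The team screens for risk factors, interviews only where indicated, and reviews charts that may already hold the diagnosis.
- *New diagnoses arise in BIT months only.* Usual psychiatric care continues in control months and can also add diagnoses. What matters is the difference between arms; the scenarios' one-arm labelling stands for that net difference.
- *The covariate is counted at discharge.* The 54% is a fiscal-year-2017 background statistic. Counting discharges fixes its denominator, not when a diagnosis was first recorded.
- *The bias is large.* Suppose 60% of patients truly have a condition, at 25% risk against 6.25%. If BIT months record every case and control months record 80% or 70%, the OR is 0.86 or 0.81. That needs complete recording in BIT months, control prevalences of 48% or 42% rather than 54%, and 12% or 18% of all patients newly labelled.

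**Conclusion.** The point holds as a conditional one. As written, the model permits adjustment for diagnoses recorded after exposure, and the arms differ by design in psychiatric case-finding. If BIT months record more diagnoses, the adjusted OR is biased towards the BIT. If recording is equal, this bias is absent.

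The size rests on assumed labelling shares and risks: about 0.84–0.98 under no effect for 3–10% newly labelled, and about 0.93 in the central case. At 3% the bias is small. No scenario reaches 0.67, so this alone would not produce the planned effect, though it could exaggerate a modest or absent one. The article does not show that the bias will occur. It leaves the route open where a simple rule would close it.

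**What to change.** Add one clause to the model specification: psychiatric-diagnosis and comorbidity covariates come from records dated before arrival on the study unit (prior encounters, problem list, admission entry), and diagnoses first recorded during the stay are excluded. If the full protocol or analysis plan already says this, one confirming sentence is enough.

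Also tabulate new in-stay psychiatric diagnoses by arm as a process measure. That table would show directly whether ascertainment differed.

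The cost is a date filter in the EHR query and a covariate that predicts slightly less well. Enrolment has ended, but this is a definition for the analysis and needs no new data collection. It should be settled before outcomes are compared by arm.
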